## Primary efficacy dataset: Full Analysis Set (FAS)

Full analysis set (FAS) (primary analysis set) – all patients who are randomised to investigational product, excluding:

- all patients who do not receive at least one dose of investigational product;
- all patients who violate a major entry criterion; the major entry criteria are defined as follow:
  - Correct diagnosis defined by inclusion criteria 2: “Documented stage IV NSCLC as defined by IASLC Lung Cancer Staging Project (7th edition) or recurrent stage I-III disease at least 6 months after resection or after the end of adjuvant chemotherapy or after standard locoregional treatment as defined by the American College of Chest Physicians”
  - Disease control after the completion of platinum-based first-line chemotherapy defined by inclusion criteria 3: “Patients treated with 4 cycles platinum based 1st line chemotherapy as defined by the American College of Chest Physicians (i.e. radiotherapy are not allowed except palliative radiotherapy of bone metastasis)” and inclusion criteria 6: “CR, PR, or SD according to RECIST criteria after the completion of platinum-based first-line chemotherapy”
  - Correct laboratory conditions for eligibility of the trial therapy defined by inclusion criteria 4: “Documented HLA-A*0201 positivity, as determined by a local laboratory” and inclusion criteria 5: “TERT-positive NSCLC, as assessed by a central laboratory; for this, availability of adequate tissue biopsy from the primary tumor, lymph nodes or distant metastases is a prerequisite”

Patients in one or more of these 3 categories will only be excluded from the FAS if it can be clearly justified that their exclusion does not introduce bias. Patients in the FAS will be analysed according to the treatment administered at the first injection and their correct strata, provided that, in the case where the actual treatment/strata differ from the randomised treatment/strata, it can be clearly justified that this difference was not influenced by knowledge of the assigned treatment.

## Per-protocol (PP) dataset

Per-protocol (PP) analysis – all patients in the FAS who satisfy the following criteria:

- no major protocol deviations;
- good treatment compliance (early treatment discontinuations will only be considered for exclusion from the PP dataset if the reasons for early treatment discontinuation are unrelated to the assigned treatment).

## Safety (SAF) dataset

The safety dataset will include all patients who received at least one injection of investigational product.

In the event of subjects having received treatments that differed from those assigned according to the randomisation schedule, then the safety analyses should be conducted according to the treatment actually received (As Treated analysis) rather than according to the randomisation groups.

# Endpoints for analysis

## Efficacy endpoints

### Primary efficacy endpoint(s)

The primary endpoint of the study is the overall survival. Overall survival is defined as the time from the date of randomisation to the date of death.

### Secondary efficacy endpoints

Secondary endpoints of the study are:

- Survival rate at 12 months
- Time to Treatment failure

## Safety endpoints

The safety and tolerability will be evaluated by the monitoring of physical examinations, vital signs, electrocardiogram, the occurrence of AEs and SAEs, ECOG performance status, clinical laboratory evaluation and concomitant medication.

### Adverse events

Any untoward medical occurrence in a patient or clinical investigation patient administered a pharmaceutical product and which does not necessarily have to have a causal relationship with this treatment.

An Adverse event (AE) can therefore be any unfavorable and unintended sign (including an abnormal laboratory finding), symptom, or disease (new or exacerbated) temporally associated with the use of a medicinal product, whether or not considered related to the medicinal product. The events occurring during pre-and post-treatment periods will also be designated as AEs. Therefore, reporting of such events, AEs and SAEs, will commence when the patient is enrolled into the study (date of signature of the informed consent) up until 4 weeks after the end of the treatment visits.

Adverse events (AE) will be coded using the latest available version of the Medical Dictionary for Regulatory Activities (MedDRA) and will be classified by MedDRA Preferred Term (PT) and System Organ Class (SOC).

Treatment Emergent Adverse Events (TEAE) will be defined as any adverse event that occur or worsen after the start of the study treatment *i.e.:*

- An AE that was not present prior to receiving the beginning of study treatment, or
- An AE that was present prior to receiving beginning of study treatment but which made the condition worse after the study treatment started.

Serious adverse events (SAE) are those AE that put the life of the patient at risk or that cause serious or permanent damage to the patient's health. An AE is to be recorded and reported as SAE in the event of any of the following:

- AE results in death
- AE is life-threatening
- AE requires hospitalisation or prolongation of existing hospitalisation
- AE results in persistent or significant disability or incapacity
- AE is a congenital anomaly or birth defect.
- AE is another medically important condition: This refers to an AE that may not be immediately life-threatening or results in death or hospitalization but may jeopardize the patient or may require intervention to prevent one of the outcomes listed above. Based on medical and scientific judgment (according to the investigator and or the sponsor) this should usually be considered serious.

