The maximum duration of the treatment period for any patient for this study (comprising of the entire period of vaccinations until progression or withdrawal for any other reason) will be no more than the duration of the study. The duration of active follow up for survival and disease recurrence related to study participation will be dictated by the completion of the final analysis. Upon completion of the final analysis and if appropriate, patients under active treatment will continue to receive Vx-001 (the ARG-Vx001 peptide) within the remit of the study, until disease progression or marketing authorization of the vaccine and at the latest until the end of 2018. During this period patients will be followed-up every 12 weeks as described in the protocol. Patients under placebo treatment will stop to receive placebo and must undergo a complete final study termination visit and enter in the follow-up period for collection of survival data.

Treatment administration and duration:

- Investigational product:

Patients receive two vaccinations with 2mg TYR-Vx001 (weeks 0, 3), four vaccinations with 2mg ARG-Vx001 (weeks 6, 9, 12, 15) followed by vaccinations with 2mg ARG-Vx001 every 12 weeks commencing at week 27 until disease progression. If appropriate, patients, that have not progressed, will continue to receive Vx-001, until disease progression, unacceptable adverse events, death, major protocol violation, withdrawal of consent, or other reason as study closure.

Solutions for injection of Vx-001 peptides will be emulsified with adjuvant Montanide ISA51™ just prior to injection and will be administered subcutaneously.

- Reference therapy: Placebo:

Patients receive two subcutaneous injections with TYR-Vx001 Placebo at weeks 0, 3, followed by four vaccinations with ARG-Vx001 Placebo (weeks 6, 9, 12, 15) followed by injections of ARG-Vx001 Placebo at 12-week intervals commencing at week 27 until disease progression, unacceptable adverse events, death, major protocol violation, withdrawal of consent, or other reason as study closure, or study unblinding, if earlier.

Placebo solutions for injection will be emulsified with Montanide ISA51™ and will be administered subcutaneously.

The vaccination schedule is detailed in Figure 1.

Figure 1: Detailed schedule of vaccinations

Randomization:

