| **Time (weeks)** |  | Up to 3 weeks after last chemotherapy administration | 0 | 3 | 6 | 9 | 12 | 15 | 18 weeks | 27, 52, 75, and every 24 weeks until EOT | 39, 63 and every 24 weeks until EOT | Final visit | Survival follow-up |
| **Vaccination** |  |  | **_TYR-Vx001_** | **_TYR-Vx001_** | **_ARG-Vx001_** | **_ARG-Vx001_** | **_ARG-Vx001_** | **_ARG-Vx001_** |  | **_ARG-Vx001_** | **_ARG-Vx001_** |  |  |
| **Eligibility** | Informed consent | X | X^1^ |  |  |  |  |  |  |  |  |  |  |
|  | Inclusion/exclusion criteria | X | X |  |  |  |  |  |  |  |  |  |  |
|  | Blood sample for HLA typing | X |  |  |  |  |  |  |  |  |  |  |  |
|  | Tumour sample for TERT and biomarker | X |  |  |  |  |  |  |  |  |  |  |  |
|  | Allocation of IWRS subject number | X |  |  |  |  |  |  |  |  |  |  |  |
| **Randomization** | Randomization |  | X |  |  |  |  |  |  |  |  |  |  |
| **Study Drug** | **Vx-001 - Placebo** |  | X | X | X | X | X | X |  | X | X |  |  |
| **Safety** | Urinary pregnancy test |  | X |  |  |  |  |  |  |  |  | X^2^ |  |
|  | Demography, medical and treatment history |  | X |  |  |  |  |  |  |  |  |  |  |
|  | Physical exam, vital signs |  | X | X | X | X | X | X | X | X | X | X |  |
|  | ECOG Performance Status |  | X |  |  | X |  |  | X | X |  | X |  |
|  | Injection-site inspection |  | X | X | X | X | X | X | X | X | X | X |  |
|  | Body weight  (height at baseline) |  | X |  |  |  |  |  | X | X | X | X |  |
|  | 12-Lead ECG |  | X |  |  |  |  |  | X |  |  | X |  |
|  | Adverse Events/Toxicity assessments | X**** | X | X | X | X | X | X | X | X | X | X |  |
|  | Record concomitant medications |  | X | X | X | X | X | X | X | X | X | X |  |
|  | Haematology^3^ & clinical chemistry^4^ |  | X^6^ |  |  | X |  |  | X | X | X | X |  |
| **Efficacy** | Chest /abdomen CT or MRI | X** |  |  |  |  |  |  |  |  |  |  |  |
|  | Bone scanning^5^ | X |  |  |  |  |  |  |  |  |  |  |  |
|  | Blood sample (immunomonitoring) and biomarkers)^7^ |  | X |  | X |  |  |  | X |  | X | X^8^ |  |
| **Survival** | Record post-study treatments and responses |  |  |  |  |  |  |  |  |  |  |  | X |

.

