**Adverse events tabulations:**

Tabulation of adverse events will present for each cell the following information: number of patients with at least one occurrence of the event, corresponding percentage and number of events (if relevant). The following tables will be produced for all subjects included in the SAF population as well as by treatment group:

Summary table of adverse events (Statistical Table 32):

- Any AE
- Any TEAE
- Any drug-related TEAE
- Any TEAE leading to study drug discontinuation
- Any SAE
- Any treatment emergent SAE

For each category of the summary table of AE, 95% confidence intervals will be calculated for the incidence rates in each treatment group, together with a confidence interval for the treatment group difference in incidence rates.

A descriptive analysis will be performed for TEAEs. Global frequencies of SOC and PT will be calculated for:

- All TEAE by SOC an PT (Statistical Table 33)
- All not related TEAEs (*i.e.,* causality relationship to study drug is Not related) by SOC and PT (Statistical Table 34)
- All related TEAEs (*i.e.,* causality relationship to study drug is Possible, Probable or Definite) by SOC and PT (Statistical Table 35)
- All TEAEs by SOC and PT and by severity grade (Statistical Table 36)

Multiple counts within a PT or SOC (repeated or different included terms or changes in descriptors) will be considered only once per subject for the calculation of frequencies.

Depending on the number of TESAEs, similar tables as described above for TEAEs may be produced for TESAEs (Statistical Table 37, Statistical Table 38, Statistical Table 39 and Statistical Table 40). If the number of TESAEs is small, no specific tabulation of TESAEs will be produced.

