**Missing or incomplete dates**:

For all listings, missing or incomplete dates will be left as they were recorded.

For calculation / sorting / assignation based on dates (e.g. treatment emergent AEs, concomitant medications…), the following rules will apply:

- The most conservative approach will be considered (i.e. if the onset date of an AE/concomitant medication is missing / incomplete, it will be assumed to have occurred during the study treatment phase (*i.e.* a TEAE for AEs) except when the partial onset date or other available data indicate differently (*e.g.* start date day missing, but month before the month of baseline date, or stop date before baseline date).
- Medical history or disease diagnosis with missing/incomplete date will be assumed to have occurred before any study treatment except when the partial onset date or other available data indicates differently.
- Assignations based on dates will be reviewed and confirmed or infirmed during the data review meeting

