### Interim Analyses and Data Monitoring

No Data and Safety Monitoring Board has been set-up for this study.

The primary study analysis will be performed when all patients randomised will have reached 6 months follow-up. A long term follow-up analysis will be performed later when the follow-up of the study will be completed.

Two database locks will be performed. The first lock will occur for the primary study analysis. Before this first database lock, the data will be reviewed and the classification of protocol deviations will be done during the Blind data review meeting. After the first database lock, all study personnel will have access to unblinded data.

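### The TEAE definition borrows its end from the AE reporting window, does not deal with later anti-tumour therapy or second-lock data, and feeds a crude arm comparison that ignores unequal exposure

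*SAP*

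**What the plan says.** In the SAP section on adverse events under the safety endpoints, "Treatment Emergent Adverse Events (TEAE) will be defined as any adverse event that occur or worsen after the start of the study treatment". The two bullets that follow restate the start condition and add no end. The same section says that "The events occurring during pre-and post-treatment periods will also be designated as AEs" and that AEs and SAEs are reported from consent "up until 4 weeks after the end of the treatment visits".

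The schedule of assessments marks the row "Adverse Events/Toxicity assessments" from screening to the end-of-treatment visit and leaves the post-treatment follow-up column blank. For an AE with a missing onset date, section 5.3.2 says that "it will be assumed to have occurred during the study treatment phase", and treats this as equivalent to a TEAE.

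The summary of adverse events (Statistical Table 32, section 5.2.5) gives 95% confidence intervals for incidence in each arm, "together with a confidence interval for the treatment group difference in incidence rates".

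After the final analysis Vx-001 may continue, if appropriate, until the end of 2018 at the latest. By contrast, "Patients under placebo treatment will stop to receive placebo"; the description of the reference therapy also ends placebo at study unblinding if that comes sooner. Section 5.3.3 plans two locks and a later long-term analysis, and states: "After the first database lock, all study personnel will have access to unblinded data".

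**The concern.** Comparing the safety of Vx-001 and placebo is a stated objective, and the SAP records that no data and safety monitoring board was set up. The AE tables therefore carry much of the safety conclusion. Three features weaken the comparison.

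- **Later therapy.** Progression is the first listed reason for stopping, and further treatment may then follow local standard of care. Toxicity of that treatment, if it falls in the reporting window, is attributed to the study arm.
- **Second lock.** If the AE tables are rerun for the long-term analysis, all new on-treatment time comes from one arm and causality is judged with the allocation known.
- **Unequal exposure.** Treatment continues to progression. An arm that stays on treatment longer has more time to record a first event, so a crude percentage can rise without any greater toxicity.

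**Working it through.** **Where the TEAE period ends.** The definition supplies only a start. TEAEs are a subset of recorded AEs, and recording stops 4 weeks after the end-of-treatment visits, with no AE assessment scheduled in survival follow-up. The effective limit is therefore the end-of-treatment visit plus 4 weeks. The SAP writes such a limit explicitly for concomitant medication (section on prior and concomitant medication) but not for TEAEs.

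**Later anti-tumour therapy.** Nothing in the TEAE definition or in section 5.2.5 removes or flags events that begin after another anti-tumour therapy starts. Such events count if that therapy starts before a late end-of-treatment visit or within the 4 weeks after it. The SAP does treat this date as a break elsewhere: initiation of other anti-tumour treatment is a failure event for time to treatment failure (section 5.2.4.3). How many TEAEs are involved cannot be calculated from the document.

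**Unblinding.** The section on blinding places final unblinding after the primary-analysis lock, and section 5.3.3 agrees. First-lock tables therefore hold no events from after the final unblinding. Between the two locks placebo has stopped and Vx-001 may continue. Section 5.2.5 does not restrict the AE tables to first-lock data, and section 5.3.3 does not describe the safety content of the later analysis.

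**Unequal exposure: an illustration.** The SAP gives no figure for time on treatment or AE rates, so these are assumed.

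- From the SAP: 12-month survival of 43% and 58%, with exponential medians stated as 9.8 and 15.2 months. Check: 12 × ln2 / (−ln 0.43) = 9.86 and 12 × ln2 / (−ln 0.58) = 15.27, in line with the stated values. The ratio is 15.2/9.8 = 1.551.
- Assumed: exponential time on treatment with a placebo median m of 3, 4 or 6 months; Vx-001 median 1.551 × m; the same rate λ of first events in both arms, 0.03, 0.05 or 0.10 per patient-month.

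With μ = ln2 / median, the probability of a first event while on treatment is λ / (λ + μ).

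For m = 4 and λ = 0.05:
- Placebo: μ = 0.6931/4 = 0.1733; 0.05/0.2233 = 22.4%.
- Vx-001: median 6.20, μ = 0.1117; 0.05/0.1617 = 30.9%.
- Difference: 8.5 points with identical toxicity.

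Differences over the grid, in percentage points:

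| Placebo median | λ = 0.03 | λ = 0.05 | λ = 0.10 |
| --- | --- | --- | --- |
| 3 months | 5.3 | 7.3 | 10.0 |
| 4 months | 6.4 | 8.5 | 10.6 |
| 6 months | 8.1 | 10.0 | 10.9 |

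Adding the 4-week reporting tail (28 days, about 0.92 months) to both arms multiplies each difference by exp(−0.92λ). The 8.5 points become 8.5 × 0.955 = 8.1, and the range becomes 5.3 × 0.973 = 5.1 to 10.9 × 0.912 = 9.9. If treatment is not prolonged, μ is equal in the two arms and the difference is zero.

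**The case against.** The strongest reply is that the plan does have an end to the TEAE period, through data collection. That is correct. A reader might infer from the definition alone that all second-line toxicity during survival follow-up is tabulated; the 4-week reporting limit and the blank follow-up column rule this out. The route for second-line toxicity is narrow, and the document allows no estimate of its frequency or of the direction of any bias.

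A reader might also infer that post-unblinding events distort the planned primary safety comparison. The order of lock and unblinding excludes this. Nothing says that the comparative tables will be rerun after the second lock, and continued Vx-001 is itself conditional. The point is that the SAP does not settle the matter beforehand.

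Nor does the 22.4% against 30.9% illustration measure the effect of the missing end point. It contains no second-line toxicity and no post-unblinding events, and closing the window would not remove the difference. It shows only the effect of unequal exposure. Its inputs are also open to challenge: applying a ratio of assumed survival times to treatment time is an assumption, and a constant event rate fits poorly with six injections by week 15 followed by one every 12 weeks from week 27.

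Finally, the SAP has partial safeguards. Exposure is summarised by arm (Statistical Table 31), related and unrelated TEAEs are tabulated separately (Statistical Tables 34 and 35), and the AE listings show onset, time since last vaccination and causality. Crude percentages beside an exposure table are common practice. These let a careful reader notice an imbalance, but they do not adjust the interval for the difference in Statistical Table 32 or separate events by the start of later therapy.

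**Conclusion.** The concern holds in limited form, at low to moderate severity. The TEAE definition relies on the reporting window for its end; events after other anti-tumour therapy within that window count as TEAEs; and no AE cut-off governs tables produced after the second lock.

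The crude comparison in Statistical Table 32 is a separate weakness and applies already at the first lock. Its size depends on assumed time on treatment, assumed event rates and assumed prolongation by 15.2/9.8: about 5 to 11 points over the range examined, and nil without prolongation. The contributions of second-line toxicity and of post-unblinding dosing cannot be quantified from the document.

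The safety tables and their confidence intervals are affected. The primary overall survival test is not.

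**What to change.** - State the end of the TEAE period in the definition: 4 weeks after the end-of-treatment visit, matching the reporting window.
- Tabulate separately the AEs that start after another anti-tumour therapy begins.
- Limit between-arm AE comparisons to data before unblinding, and report later Vx-001 events descriptively only.
- Beside the crude percentages in Statistical Table 32, add events per patient-year, with time at risk defined by the same window.

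The cost is SAP wording, one additional table and a few columns. The start of other anti-tumour treatment is already needed for time to treatment failure, and treatment duration is already derived for Statistical Table 31.

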### Laboratory endpoints

The following clinical laboratory parameters will be measured at Baseline, week 3, week 6, week 9, week 12, week 15, week 18, every 12 week from week 27 to week 75 and every 24 week until End of treatment:

- Hematology: Hemoglobin, Hematocrit, WBC, Neutrophils, Lymphocytes, Monocytes, Eosinophils, Basophils and Platelet count
- Clinical chemistry: Sodium, Potassium, Calcium, Glucose, BUN or urea, Creatinine, AST, ALT, Alkaline phosphatase, Total bilirubin, Total protein, Albumin, LDH and Gamma-GT

### Other safety endpoints

#### **Physical examination and Vital signs**

A physical examination and vital signs will be conducted and recorded in the eCRF at Baseline, week 3, week 6, week 9, week 12, week 15, week 18, every 12 week from week 27 to week 75 and every 24 week until End of treatment.

Any physical examination abnormalities noted at baseline will be recorded and re-assessed at subsequent evaluations. All newly- diagnosed or worsening conditions or signs and symptoms observed after baseline evaluation, irrespectively of whether related to treatment or not, will be recorded as AEs.

Vital signs will include:

- blood pressure
- pulse rate after 5 minutes sitting,
- body temperature,
- weight, height (only at baseline).

#### **ECG**

A 12-lead ECG will be performed at baseline, week 18 and final visit (End of treatment visit)

#### **ECOG**

The ECOG performance status will be determined and recorded in the eCRF at Baseline, week 9, week 18, every 12 week from week 27 to week 75 and final visit.

The ECOG performance status will be graded according the following criteria:

- Grade 0: Fully active, able to carry on all pre-disease performance without restriction
- Grade 1: Restricted in physically strenuous activity, but ambulatory and able to carry out work of a light or sedentary nature, e.g., light house work, office work
- Grade 2: Ambulatory and capable of all selfcare, but unable to carry out any work activities. Up and about more than 50% of waking hours
- Grade 3: Capable of only limited self-care, confined to bed or chair more than 50% of waking hours
- Grade 4: Completely disabled. Cannot carry on any self-care. Totally confined to bed or chair
- Grade 5: Dead

